### 9.1.3 General Considerations on Data Analysis.

Sensitivity analyses using information provided by the study questionnaire about sexual activity, immunological status, concomitant medication and other will be performed when necessary.

Significant difference in the infectivity rate will be accepted with a p-value <0.05.

A partial analysis after completing 50% of the planned recruitment and a global analysis at the end of the 7-month follow-up will be carried out.

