## 9 STATISTICAL ANALYSIS PLAN

### 9.1 Study Objectives, Endpoints and Data Analysis

#### 9.1.1 Primary Objective

##### 9.1.1.1 Objective 1

To demonstrate that vaccination with a 3-dose regimen of 9vHPV will reduce viral infectivity in cervical, anal, urine, vulvar and oral samples from HPV 16/18/16+18-positive women.

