#### **9.1.1.2 Data analysis**

Differences in the infectivity rate before (Day 1/ Visit 1) and after vaccination (Month 7/ Visit 4) will be compared in cervical, anal, vulvar, urine and oral samples using non-parametric Wilcoxon signed rank test.

For cervical samples, joint and stratified analysis for HPV-RIFT1 and HPV-RIFT2 cohorts will be done.

Oral, vulvar, urine and anal samples included in the HPV-RIFT1 and HPV-RIFT2 cohorts will be analyzed together to obtain the minimal sample size established for this analysis. If sample size would allow stratified analysis for HPV-RIFT1 and HPV-RIFT2 cohorts, it will be performed and submitted.

Sensitivity analysis including only cases showing negative seroconversion before vaccination will be performed.

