## 9.2 Sample Size and Power

### 9.2.1 RIFT-HPV 1 cohort

The sample size for this cohort has been calculated based on the demonstration of viral infectivity reduction before and after a 3-dose regimen of 9vHPV vaccination in cervical samples as a reference.

Accepting an alpha risk of 0.05 and a beta risk of less than 0.2 in a bilateral contrast, it has been estimated that a minimum of 39 women fulfilling the 3-dose vaccination schedule is needed to detect a difference equal to or greater than a 25% infectivity reduction in cervical samples.

It has been estimated a 40% sampling loss from those study subjects:

- showing an HPV16/18/double 16-18 positive result not confirmed by Anyplex HPV28,
- not fulfilling the 9vHPV 3-dose schedule,
- showing HPV clearance at Month 7 visit,
- showing a non-productive infection before vaccination.

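### One flat p<0.05 covers five sample types and per-cohort cervical tests with no rule for which result meets the primary objective, and the 50% analysis has no stated role or threshold

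*Protocol*

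**What the plan says.** The primary objective in protocol section 9.1.1 is "To demonstrate that vaccination with a 3-dose regimen of 9vHPV will reduce viral infectivity in cervical, anal, urine, vulvar and oral samples". Section 9.1.1.2 says that Visit 1 and Visit 4 infectivity rates "will be compared in cervical, anal, vulvar, urine and oral samples using non-parametric Wilcoxon signed rank test".

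On cohorts, the same section says: "For cervical samples, joint and stratified analysis for HPV-RIFT1 and HPV-RIFT2 cohorts will be done". Oral, vulvar, urine and anal samples from both cohorts "will be analyzed together to obtain the minimal sample size established for this analysis". Strata for these four are conditional: "If sample size would allow stratified analysis for HPV-RIFT1 and HPV-RIFT2 cohorts, it will be performed and submitted".

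Section 9.1.3 sets the criterion, "Significant difference in the infectivity rate will be accepted with a p-value <0.05", and its next sentence announces "A partial analysis after completing 50% of the planned recruitment and a global analysis at the end of the 7-month follow-up". It does not say what the partial analysis tests, at what level, or what may follow from it.

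Sections 9.2.1 and 9.2.2 size the study on cervical samples (39 women, 25% reduction) and anal samples (28 women, 35% reduction), each on the same terms: "Accepting an alpha risk of 0.05 and a beta risk of less than 0.2 in a bilateral contrast". No size is given for vulvar, urine or oral samples.

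**The concern.** The objective is to demonstrate an effect, yet a reader cannot tell from section 9 which result would demonstrate it. At least seven tests are definite at the final analysis: five sites, plus the two cervical cohort strata. All share one threshold. A half-way analysis follows in the next sentence with no threshold of its own.

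Section 4.2.1 says the results can supply the proof of concept that may support vaccinating adult women. The study has no control group. With no success rule fixed in advance, one nominally significant fluid could be presented as meeting the primary objective, with a false-positive risk well above the 5% used in the sample size.

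The minimal-size sentence in section 9.1.1.2 adds to this. It lets vulvar, urine and oral samples appear to be sized for a test when section 9.2 does not size them.

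**Working it through.** **The plan's own figures.** The protocol states no family-wise error, so there is none to reproduce. Its sizes show which fluids were planned for:

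- Anal: 30 × 0.60 = 18 women from RIFT-HPV 2, plus 10 from RIFT-HPV 1 (39 × 0.28 = 10.9, taken as 10), gives 28. This pooled minimum does exist.
- Cervical: 39 is stated without a standard deviation for the paired difference. It can only be back-solved, giving an SD of about 0.56 for a 25% reduction.
- Vulvar, urine, oral: nothing to reproduce.

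**Inputs from the protocol.** Threshold 0.05, two-sided; five sites; joint plus two cohort strata for cervical samples; cohort sizes 39 and 30, used as stratum weights; one partial analysis at 50% of recruitment.

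**Assumptions not in the protocol.** Any one significant result suffices. The partial analysis tests infectivity at 0.05, at information fraction 0.5. Between-site correlation is 0, 0.5 or 0.9, since all samples come from the same women.

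**Five sites, final analysis, independent.** 1 − 0.95^5 = 1 − 0.774 = 22.6%.

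**Correlation, strata and look.** These come from simulation of normal test statistics, 400,000 runs. The joint cervical statistic is √(39/69)·z₁ + √(30/69)·z₂. The final statistic is √0.5·z(first half) + √0.5·z(second half).

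| Tests counted, two-sided | Corr. 0 | Corr. 0.5 | Corr. 0.9 |
|---|---|---|---|
| Five sites, final only | 22.6% | 18% | 10% |
| Plus two cervical strata | 28% | 23% | 15% |
| Five sites, half-way and final | 35% | 29% | 16% |
| Sites, strata and both looks | 42% | 36% | 24% |

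Treating the seven final tests as independent would give 1 − 0.95^7 = 30.2%. That is too high, because the strata are parts of the joint cervical test.

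**One site tested twice at 0.05.** 8.3% at information fraction 0.5. Fewer than half of the Month 7 results may exist at half of recruitment; at fraction 0.25 the figure is 9.1%.

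**False claims of reduction only.** Each two-sided test allows 2.5% in that direction. Five independent sites give 1 − 0.975^5 = 11.9%. Sites, strata and both looks together give 24% if independent, 18% at correlation 0.5 and 12% at 0.9.

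**All five sites required.** The chance that every site is falsely significant cannot exceed the chance for one, 5%, so testing several sites does not inflate the error.

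**The case against.** Four points deserve weight.

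*The success rule is unstated, not stated as any-site.* The objective joins the five sites with a plain conjunction, which can be read as requiring all of them. A reader might infer that one significant fluid, at either look, would be reported as meeting the objective. The protocol does not say so. It leaves this possible and does not exclude it. This stands, and every inflated figure above is conditional on it.

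*The partial analysis may test nothing.* Section 9.1.3 says only that it takes place. A reader might infer a false-claim risk of about one in three from the 35% figure. The documents do not support that as a headline: it needs an any-site rule, a half-way test at 0.05, independent sites and significance counted in either direction. It is not a ceiling either, because it leaves out the cervical strata.

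*The minimal-size wording has a basis for anal samples.* Section 9.2.2 reaches 28 by pooling cohorts. This stands, so the fault is limited to vulvar, urine and oral samples. A reader might go further and infer that these fluids will have too few pairs for significance. An exact two-sided signed-rank test cannot reach 0.05 with five pairs (2 × 0.5^5 = 0.0625), and section 8.2.2.4 expects low viral load in oral samples. But no passage gives an expected number of pairs, so that conclusion does not follow.

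*This is a proof-of-concept study, and a separate analysis plan may exist.* Strict family-wise control is less clearly required here than in a confirmatory trial. However, the objective is worded as a demonstration, section 9 is itself titled as the statistical analysis plan, and it fixes the threshold. A later document would have to alter a stated rule as well as add detail.

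**Conclusion.** The point holds in a conditional form. The protocol fixes one unadjusted threshold for five sites and the cervical cohort tests under one primary objective, without saying which result meets that objective, and adds a half-way analysis with no defined role.

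The figure that needs the fewest assumptions is the one for five sites at the final analysis, if any site suffices: about 23% with independent sites and 10–18% at correlation 0.9–0.5. Larger figures, up to about 42%, also require an unadjusted half-way test and counting the cervical strata. Conditional cohort strata for the other four fluids are not counted. In the direction of interest alone, the range with independent sites is about 12% to 24%.

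Separately, and without any assumption, section 9.1.1.2 refers to an established size that section 9.2 does not give for three of the four fluids it covers.

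**What to change.** In sections 9.1.1.2 and 9.1.3:

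1. Name the cervical comparison, Visit 1 against Visit 4 with both cohorts pooled, as the first confirmatory test at two-sided 0.05 on the final data.
2. Test pooled anal samples at two-sided 0.05 only if the first test is significant.
3. Report vulvar, urine and oral results and all cohort strata as estimates with confidence intervals, without a confirmatory claim.
4. State that the 50% analysis is descriptive, makes no significance test of infectivity and changes nothing in the trial.
5. Limit the minimal-size wording to anal samples.

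This holds the family-wise error at 5% and leaves the alpha behind the sizes of 39 and 28 unchanged. Splitting alpha instead gives 0.05/5 = 0.01 per site. Power at the planned sizes then falls from 80% to about 59%, and restoring it takes ((2.576 + 0.842)/(1.960 + 0.842))² ≈ 1.49 times the numbers: 39 becomes about 58 and 28 about 42.

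The cost is more than wording. Three fluids named in the primary objective lose confirmatory status. The anal claim, for which RIFT-HPV 2 was sized, depends on the cervical result: with 80% power for each and independence, both succeed in 0.8 × 0.8 = 64% of trials, and more often with positive correlation. A protocol amendment may be needed, and section 10.1 sends substantial ones for ethics and regulatory approval. No new subjects or assays are required. A smaller repair, naming one lead site or stating an all-sites rule, would settle the success rule but still leave the 50% analysis and the size wording to correct.

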### 9.1.4 Definitions Regarding Data Description and Analysis.

**Infectivity rate:** The infectivity rate of cervical, anal, urine, vulvar and oral samples collected from study subjects before and after 9vHPV vaccination will be obtained measuring the in-vitro expression of HPV biomarker E1E4 mRNA in HaCaT keratinocytes incubated during 24h with study samples (quantitative variable). The expression level of a positive control sample and the human gene HPRT1 will be used to normalize the expression measurements. The quantity of HPV-infected keratinocytes (i.e., expressing E1E4 mRNA) will be directly proportional to the quantity of free HPV viral particles present in samples (i.e. not neutralized by HPV antibodies). Reduction in infectivity will be expressed as the difference between the infectivity rate of cervical, anal, urine, vulvar and oral samples before and after the subject receives 9vHPV vaccination.

**HPV persistent infection:** an HPV infection of the same genotype and sample type (oral, anal, urine, vulvar or cervical) detected in samples collected at Day1/Visit 1 and Month 7/Visit 4 is defined as persistent infection (qualitative variable: persistent or non-persistent infection).

**HPV productive infection:** an HPV positive infection that produce new viral particles detected by immunoassays or EM in oral, anal, urine, vulvar or cervical samples is defined as productive infection (qualitative variable: presence or absence of viral particles).

**Positive/negative HPV seroconversion:** it is defined as the status of study serum samples regarding presence (positive) or absence (negative) of type-specific HPV antibodies. Positive seroconversion may occur after administration of study vaccine, or by subject's natural immunological response to a previous HPV infection. Negative seroconversion may occur when study vaccine fails to trigger an immunological response in the subject. Quantitative results of the HPV antibodies detection test are reported in terms of arbitrary units (milliMerck units/ml). Results may be reported qualitatively as positive or negative seroconversion for type-specific HPV antibodies.

**Anti-HPV antibodies exudation:** type-specific HPV antibodies will be detected in cervical, anal, urine, vulvar and oral samples (cLIA/ ELISA), and results will be expressed qualitatively as antibody presence or absence.

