### **8.2.2 Laboratory Procedures**

#### **8.2.2.1 HPV Infective Capacity In-Vitro Evaluation: E1^E4-HaCaT Essay**

The functional HaCaT-E1^E4 model will be used to assess and quantify the infectivity of body fluids samples from HPV-positive study subjects. Briefly, the assay consists in quantifying the levels of HPV E1^E4 mRNA present in HaCaT cell cultures exposed to HPV-positive exudates, since the expression of HPV E1^E4 mRNA is a surrogated marker that correlates with the number of keratinocytes that have been infected.

For the analyses, 20,000 HaCaT keratinocytes will be grown in 6-well plates until they reach sub-confluent status. Then, cells will be exposed to 0,5 mL of cervical, anal, urine, vulvar and oral samples or PBS (negative control) for 24 hours. After the incubation period, cultured cells will be washed with PBS buffer and recovered after treatment with trypsin in a 15 mL Falcon tube. Finally, cells will be pelleted by centrifugation and stored at -80°C until gene expression analyses.

For the assessment of HPV E1^E4 mRNA expression, two different gene expression analyses will be performed: RT-qPCR using TaqMan assays and in situ RNA hybridization using fluorescent RNAscope probes.

Total RNA from samples and negative controls will be isolated using RNeasy kit (Qiagen) and reverse transcribed to cDNA with High-Capacity cDNA Reverse Transcription kit (Applied Biosystems). Quantification of E1^E4 mRNA levels will be done by real-time qPCR on a CFX96 instrument (BioRad) and type-specific TaqMan assays (Applied Biosystems) for HPV 11/16/18/31 genotypes will be used.

TaqMan assays consist of a pair of unlabeled PCR primers and a probe labelled with a fluorophore and a quencher in its ends. As target amplification moves forward, 5'-exonuclease

activity of Taq polymerase degrades the probe annealed to the target sequence, thus releasing the fluorophore. Then fluorescence is proportional to target abundance and can be measured by the CFX96 instrument, obtaining a Ct value that estimates the initial amount of target cDNA copies.

TaqMan assays targeting housekeeping genes B2M and GAPDH will also be used as normalizers for relative quantification by comparison of Ct values.

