##### 9.1.1.1.2 *Inclusion in the analysis population*

The below criteria will be followed to include cases in the analysis population:

Before vaccination (Visit 1):

- HPV16/18/16+18 positive DNA detection and genotyping (using Anyplex HPV28) in collected cervical, anal, urine, vulvar and oral samples.
- HPV16/18 positive virion detection (using ELISA, electronic microscopy) in collected cervical, anal, urine, vulvar and oral samples.

Therefore, cases showing:

- negative HPV16/18 DNA test and/or
- absence of HPV16/18 viral particles,

will not be included in the analysis population.

After vaccination (Visits 2 to 4, Months 2, 6 and 7):

- HPV16/18/16+18 positive DNA detection and genotyping (using Anyplex HPV28) in collected cervical, anal, urine, vulvar and oral samples.
- HPV16/18 positive virion detection (using ELISA, electronic microscopy) in collected cervical, anal, urine, vulvar and oral samples.
- Positive detection of exudated HPV 6/11/16/18/31/33/45/52/58 L1 antibodies in collected cervical, anal, urine, vulvar and oral samples.
- Positive detection/titration of HPV 6/11/16/18/31/33/45/52/58 L1 antibodies in collected serum samples (positive seroconversion).

Therefore, cases showing:

- negative HPV16/18 DNA test and/or
- absence of HPV16/18 viral particles and/or

- absence of exudated HPV L1 antibodies and/or
- absence of positive seroconversion,

will not be included in the analysis population.

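### The primary analysis set does not require the baseline genotype to persist, so a 16/18 switch or partial clearance of a double infection can be read as vaccine neutralisation

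*Protocol*

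**What the plan says.** Section 9.1.1.1.2 of the Protocol sets the primary analysis set. The DNA criterion has the same wording before vaccination and at Visits 2 to 4: "HPV16/18/16+18 positive DNA detection and genotyping (using Anyplex HPV28) in collected cervical, anal, urine, vulvar and oral samples". Virions of HPV16/18 must also be found at each visit. After vaccination, antibodies must be present in the sample and in serum. A case leaves the set only if it is negative for HPV16/18 DNA or lacks virions, exudated antibody or seroconversion. Nothing links the later genotype to the genotype at Visit 1.

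Section 9.1.4 does contain a matched definition. Persistent infection is "an HPV infection of the same genotype and sample type" at Visit 1 and Visit 4. No inclusion rule or analysis in section 9 refers to it.

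Section 9.1.1.2 compares infectivity at Visit 1 and Visit 4 with a Wilcoxon signed rank test. Section 9.1.2.2.1 applies the same criteria to the 1-dose and 2-dose objective. On the readout, 8.2.2.1 says that "type-specific TaqMan assays (Applied Biosystems) for HPV 11/16/18/31 genotypes will be used". Section 8.2.2.2 gives the purpose of genotyping as telling a vaccine effect from spontaneous clearance. Section 4.1 states that there is no control group.

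**The concern.** Read literally, the rule keeps two kinds of pair in which the baseline infection has wholly or partly gone: HPV16 at Visit 1 with HPV18 at Visit 4 (or the reverse), and HPV16+18 at Visit 1 with one type left at Visit 4. In such pairs the E1^E4 signal of the lost type falls because that infection has cleared, not because antibodies blocked its virions. Genotyping is in the protocol to make this distinction, and without a control group nothing else in the design corrects for it.

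The protocol's own account makes some clearance likely. Section 2.2.7 says that most infections clear within 12 to 24 months, 5.1 admits women diagnosed up to 10 months earlier, and follow-up adds 7 months. Section 9.2.1 lists women "showing HPV clearance at Month 7 visit" among its expected losses, without saying whether clearance of one of two types counts. Double infections are eligible, because 5.1 accepts HPV16 and/or HPV18.

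**Working it through.** **Who stays in under the rule as written**

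| Visit 1 | Visit 4 | 9.1.1.1.2 | Persistent type under 9.1.4 |
|---|---|---|---|
| 16 | neither 16 nor 18 | excluded | none |
| 16 | 16 | kept | 16 |
| 16 | 18 | kept | none |
| 16+18 | 18 | kept | 18 only |
| 16 | 16+18 | kept | 16 only |

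The two sections part company in the last three rows. The other criteria do not close the gap. Virions are assessed for HPV16/18 jointly (8.2.2.4), the antibody criterion lists nine types without reference to the infecting one, and the sensitivity analyses concern serostatus (9.1.1.2) and questionnaire items (9.1.3).

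**The plan's own figure.** Section 9.2.1 states: "Accepting an alpha risk of 0.05 and a beta risk of less than 0.2 in a bilateral contrast". Its conclusion for the cervical analysis, with a 25% fall in infectivity as the target, is: "a minimum of 39 women fulfilling the 3-dose vaccination schedule is needed". No SD is given, so 39 can be neither confirmed nor refuted. From n = ((1.960 + 0.842) × SD / δ)², with n = 39 and δ = 0.25, the implied SD of the paired difference is 0.25 × √39 / 2.802 = 0.557.

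On a natural-log scale a 25% reduction is ln 0.75 = −0.288. An SD of 0.625 gives (2.802 × 0.625 / 0.288)² ≈ 37. Multiplying by π/3 for the Wilcoxon test gives about 39. The SD of 0.625 used below is therefore compatible with the stated sample size, but it remains an assumption.

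**Effect on the test when there is no neutralisation.** Inputs: n = 39 evaluable pairs (9.2.1); two-sided 5% Wilcoxon signed rank test; log ratio in matched pairs normal with mean 0 and SD 0.625; a share f of pairs mismatched. The documents do not give f, so 5%, 10% and 20% are shown (about 2, 4 and 8 of 39 pairs). They also do not fix how the type-specific readings are combined, so three readout cases were simulated with 3,000 to 4,000 replicates each:

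| Mismatched pairs | f = 5% | f = 10% | f = 20% |
|---|---|---|---|
| Only the lost baseline type is tracked (mean log ratio −4; e⁻⁴ ≈ 0.02, about 98% loss) | 8% | 17% | 50% |
| Two equal types summed, one lost (50% fall) | 6% | 8% | 20% |
| Switches without net direction (mean 0, SD 2) | 5% | 5% | 5% |

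Differences of one or two points are within simulation error.

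**Second check on another scale.** This run assumed a within-woman SD of 0.5 log10 and counted only rejections in favour of the vaccine (nominal 2.5%), again with n = 39 and f = 5%, 10%, 20%:

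- Lost baseline type tracked, 2 log10 drop: 7.2%, 17.0%, 49.9%.
- Replacing type 1 log10 lower: 6.5%, 13.4%, 38.1%.
- Two equal types summed, one lost: 3.5%, 5.1%, 10.2%.

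The pattern is the same. The readout rule matters as much as the frequency of mismatch.

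**The case against.** Four points can be made on the other side.

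- **Scope.** A reader might infer that clearance in general is counted as neutralisation. The documents do not support that. Section 9.1.1.1.2 removes any case negative for HPV16/18 DNA or without virions, and 9.2.1 allows for clearance within its loss: "It has been estimated a 40% sampling loss from those study subjects". A woman with one type who clears it, with no 16/18 replacement, is excluded. This objection stands and limits the point to switches and partly cleared double infections.
- **Direction.** A reader might also infer that the error always favours the vaccine. It need not. If readings are summed, or whichever type is present is read, a replacing or added type with a stronger signal produces an apparent increase. How readings are combined may properly be left to a statistical analysis plan that is not shown, and its absence here is not a finding. This stands too.
- **Frequency.** Section 2.2.3 says that vaccine antibodies can prevent new infections, so a switch to the other vaccine type may be uncommon. No section supports a particular mismatch share. This weakens the switch route but does not touch loss of one type from a double infection, which needs no new infection.
- **A matter for later detail.** This does not stand. The inclusion rule is written out in full in a section headed as the statistical analysis plan, and what it states disagrees with the persistence definition a few paragraphs later.

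**Conclusion.** The point holds within those limits. Followed literally, 9.1.1.1.2 puts type switches and partly cleared double infections into the primary paired test, although 9.1.4 already contains the definition that would keep them out. Partial clearance of a double infection, or tracking only the baseline type, biases towards an apparent reduction; a stronger replacing or added type in a summed readout can bias the other way.

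The size is uncertain. For 5% to 20% mismatch among 39 pairs, two-sided rejection without any vaccine effect runs from the nominal 5% to about 50%. The upper end is the least favourable readout at the highest assumed mismatch share and should not be quoted as the expected error rate. The mismatch share, the within-woman SD, the signal lost in mismatched pairs and the readout rule are all assumptions. The change should be made, because the present rule works against the stated purpose of genotyping and the correction is cheap.

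**What to change.** In 9.1.1.1.2, replace the post-vaccination DNA criterion with the persistence definition of 9.1.4: the same genotype at the same site at Visit 1 and at the visit being compared. That visit is Visit 4 for the primary objective and Visits 2 and 3 for the 1-dose and 2-dose objective, so the definition in 9.1.4 needs extending beyond Visit 4. State that the paired difference uses that genotype's own E1^E4 signal, and that in double infections only the type or types that persist are analysed.

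The cost is protocol wording and a few pairs leaving the analysis. Genotyping is already scheduled at every visit and site (1.2.2), so no new sample or assay is needed. The change does not deal with natural decline in load within a type that persists. That limitation of an uncontrolled before-and-after comparison remains and should be acknowledged when the results are interpreted.
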